### Primary outcome

The primary outcome is health status, as measured by the COPD Assessment Test (CAT)^16^ at 6 months post-baseline. This measure was chosen due to ease of use in clinical practice compared with the Chronic Respiratory Questionnaire (as used in the previous RCT). The CAT is a validated, short (eight items) and simple patient completed questionnaire and assesses globally the impact of COPD (cough, sputum, dyspnoea and chest tightness) on health status. The CAT is scored 0–5 with a range of 0–40; scores of 0–10, 11–20, 21–30, 31–40 represent mild, moderate, severe or very severe clinical impact, respectively.

### Secondary outcomes

#### Clinical measures

##### Exercise capacity

Maximal exercise capacity will be measured with the incremental shuttle walk test (ISWT) according to the protocol of Singh *et al*
17 using a 10 m course. According to current standards, an individual change of at least 47.5 m is considered clinically important.^18^ Endurance capacity will be measured with the endurance shuttle walk test using a 10 m course and a walking speed of 85% of the maximal ISWT walking speed.^19^

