### Randomisation

Once participants have consented to take part in the study and spirometry has confirmed a COPD diagnosis, participants are randomised by an unblinded member of the study team using an online randomisation tool (sealed envelope).^14^ Individuals are randomised (1:1) to the control group or the intervention (SPACE for COPD(C) group-based self-management programme) group. The system randomises patients in random permuted blocks. This allows for the 1:1 ratio, but due to the random permuted blocks of 2, 4 or 6 ensures full randomisation. Simple randomisation has been chosen as there has been no requirement to stratify by age, gender, location or other variables. Participants are immediately informed of their allocated treatment by an unblinded member of the study team. Unblinding is permissible in the case of medical emergencies (eg, cardiac arrest) or patients being admitted to hospital for an exacerbation.

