### Study outcomes

Data will be collected during baseline, 6-month and 9-month appointments at the Leicester Respiratory Biomedical Research Unit by trained members of the study team. Data are collected following standardised operating procedures. Written informed consent is obtained from all participants prior to the commencement of data collection. Details of all clinical assessments and outcome measures are provided in table 3. General practitioners are informed of patients’ participation in the trial and any relevant results. Any serious adverse events will be reported to the sponsor and patients’ ability to exercise safely will be monitored.

**Table 3 T3:** Details of study clinical assessments and outcome measures at all appointments

Baseline appointment (blinded and unblinded study team members)	6-month appointment (blinded study team member)	9-month appointment (blinded or unblinded study team member)
Consent Collection of demographic details and medical history Blood pressure Spirometry Randomisation* Questionnaires (CAT, EQ-5D, CRQ-SR, BCKQ, PAM, HADS)* Shuttle walking tests* (intervention participants only): 2xISWT; 1xESWT Participants given Senswear activity monitor to wear for 7 days*	Check consent Questionnaires (CAT, EQ-5D, CRQ-SR, BCKQ, PAM, HADS) Shuttle walking tests† Participants given Senswear activity monitor to wear for 7 days	Check consent Questionnaires (CAT, EQ-5D, CRQ-SR, BCKQ, PAM, HADS) Shuttle walking tests Participants given Senswear activity monitor to wear for 7 days

*Carried out by an unblinded member of the study team.

†ESWT carried out by an unblinded member of the study team.

BCKQ, Bristol COPD Knowledge Questionnaire; CAT, COPD Assessment Test; CRQ-SR, Chronic Respiratory Questionnaire; EQ-5D, European Quality of Life-5 Dimensions; ESWT, endurance shuttle walking test; ISWT, incremental shuttle walking test; HADS, Hospital Anxiety and Depression Questionnaire.; PAM, Patient Activation Measure.

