### Data analysis

#### Study power

The power calculation was based on the primary outcome at 6 months.^30 31^ To detect a mean±SD between-group difference of 2.5±5.0 in the change in CAT with 80% power, 60 people per group are required (α=0.05, two tailed). In anticipation of a possible 25% attrition rate, the total sample size was increased to 75 per group (150 in total).

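### No pre-treatment endurance walk speed exists for controls, so follow-up ESWT times are either referenced to different visits in the two arms or taken at a speed set after treatment

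*Protocol article*

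**What the plan says.** Under Exercise capacity, the protocol article names two walking outcomes. Maximal capacity is the ISWT, for which "an individual change of at least 47.5 m is considered clinically important". Endurance capacity is the "endurance shuttle walk test using a 10 m course and a walking speed of 85% of the maximal ISWT walking speed". No visit is attached to that maximal speed.

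Under Study outcomes, "Data will be collected during baseline, 6-month and 9-month appointments". The baseline column of Table 3 reads "Shuttle walking tests* (intervention participants only): 2xISWT; 1xESWT". The 6-month and 9-month columns list shuttle walking tests with no restriction by arm and no number of ISWTs. A footnote to the 6-month column adds "ESWT carried out by an unblinded member of the study team". The same section says "Data are collected following standardised operating procedures"; those procedures are not shown.

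**The concern.** An ESWT result is a time, and it has meaning only relative to the speed at which the patient walked. Here that speed is derived from another outcome, the ISWT, which the programme may itself change. For a clean comparison, the speed in both arms should be fixed before treatment can act on it. Table 3 rules this out for controls.

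This differs from controls simply lacking a baseline value to subtract. For ISWT distance, randomisation allows follow-up values to be compared directly. For the ESWT that remedy is not enough, because the follow-up time itself depends on which ISWT set the speed. At stake is whether the trial can say anything about the programme's effect on endurance.

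**Working it through.** The article gives no power, effect size or expected value for the ESWT, so there is no figure to reproduce. The sample-size statement concerns the CAT only.

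**Step 1: which ISWT can set the speed (Table 3 against the speed rule).**

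| Visit | Intervention arm | Control arm |
|---|---|---|
| Baseline | baseline ISWT | none |
| 6 months | baseline or 6-month ISWT | 6-month ISWT only |
| 9 months | baseline, 6-month or 9-month ISWT | 6-month or 9-month ISWT |

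At 6 months there are two pairings:

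- (a) intervention at the baseline-derived speed, controls at the 6-month-derived speed;
- (b) both arms at the 6-month-derived speed.

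At 9 months, too, every source available in both arms comes after treatment.

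**Step 2: an illustration of what the choice can do.** No input in this step comes from the documents. Assume time = D/(speed − sustainable speed) with D constant, a 240 s walk before treatment, and sustainable speed equal to a fraction c of peak ISWT speed, with c = 0.65, 0.70 or 0.75. Let peak speed change by a proportion p and sustainable speed by a proportion g. The absolute peak speed cancels, which leaves:

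- baseline-derived speed: 240 × (0.85 − c) / (0.85 − c(1+g));
- speed reset from the new ISWT: 240 × (0.85 − c) / (0.85(1+p) − c(1+g)).

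For example, with c = 0.70 and p = g = 5%, the first gives 240 × 0.15 / (0.85 − 0.735) = 313 s. The second gives 240 × 0.15 / (0.8925 − 0.735) = 229 s.

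| Assumed change | Baseline-derived speed (c = 0.65, 0.70, 0.75) | Reset speed (c = 0.65, 0.70, 0.75) |
|---|---|---|
| p = g = +5% | 287, 313, 384 s | 229 s throughout |
| p = g = +3% | 266, 279, 310 s | 233 s throughout |
| p = +5%, g = +7.5% | 317, 369, 549 s | 248, 257, 278 s |
| p = 0, g = +5% | 287, 313, 384 s | 287, 313, 384 s |
| p = g = −3% | 219, 211, 196 s | 247 s throughout |

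**Step 3: reading the table.**

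Pairing (a), with no treatment effect and the same time trend in both arms:

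- A 3% decline gives 196–219 s in the intervention arm against 247 s in controls, a spurious difference against the programme.
- A 3% rise gives 266–310 s against 233 s, a spurious difference in its favour.
- With no change in controls, resetting leaves their speed where it would have been, and this model shows no bias.

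Pairing (b):

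- If peak and sustainable speed rise in the same proportion, the gain disappears and the time falls slightly (240/1.05 = 229 s).
- If sustainable speed rises more than peak speed, part of the gain remains.
- If peak speed does not move, all of it remains.

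The seconds are very sensitive to c. At c = 0.80 and p = g = 5%, the time at the baseline-derived speed is multiplied by 0.05/0.01 = 5. The table shows that the choice matters; it does not estimate by how much.

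**The case against.** **The reference visit may be in the operating procedures.** This is a condensed article, it refers to such procedures, and it cites a source for the ESWT. The unnamed visit alone would therefore not be a finding, and that part of the objection stands. But no wording about the reference visit can supply a baseline ISWT that Table 3 does not schedule for controls.

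**The root is the one-sided baseline schedule.** True: an ISWT in every patient before randomisation would cure this and other problems. The ESWT consequence still needs stating, because comparing follow-up values alone does not rescue it.

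**Perhaps only the intervention arm performs the ESWT at follow-up.** The 6-month footnote, which assigns that test to an unblinded team member, might suggest this. There would then be no between-arm contrast, and a baseline-derived speed would give a sound within-arm change. The reading is weak: Table 3 writes the arm restriction at baseline and omits it at 6 and 9 months.

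**Two stronger inferences are not supported.** A reader might infer that pairing (a) favours the intervention. The sign depends on the time trend, which the article does not give, and a common decline reverses it. A reader might also infer that pairing (b) always cancels the gain or turns it into a loss. That follows only from letting peak and sustainable speed rise equally.

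**Conclusion.** The point holds as a defect in one secondary outcome. The article's own schedule gives controls no pre-treatment ESWT speed. Follow-up times are therefore either referenced to different visits by arm and not comparable, with bias of unknown direction, or measured at a speed set after treatment. The latter reduces a true endurance gain when peak speed has also risen, and may remove it. Neither result shows cleanly whether the programme improves endurance.

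This conclusion rests on Table 3 as printed and on controls performing the ESWT at follow-up, which is the natural reading. It does not rest on the illustrative seconds. The documents do not allow the size of the distortion to be estimated. The primary CAT comparison is untouched.

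**What to change.** Reconcile Table 3 with the Exercise capacity section:

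- State that follow-up ESWT speed is taken from the 6-month ISWT in both arms and reused at 9 months, so that the 6-to-9-month change is at constant speed.
- Describe the 6-month between-arm ESWT contrast only as endurance at 85% of current maximum. Do not use it as evidence that the programme does, or does not, improve endurance.
- Base the between-arm exercise-capacity conclusion on follow-up ISWT distance.
- Report the intervention arm's baseline ESWT descriptively.
- For tests already done, report by arm and visit which ISWT set the speed.

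This is pairing (b) with an honest label. It makes the arms use the same rule but does not recover a pre-treatment reference. Only an ISWT in all patients before randomisation would do that, and it would be an added procedure.

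The change needs protocol and operating-procedure wording and no extra visits. The price is a narrower ESWT claim and the loss of a constant-speed change from baseline in the intervention arm. One limitation remains: controls reach the 6-month ISWT without the two baseline tests that the intervention arm had, so any familiarisation effect, whose size the article does not give, would differ between arms. The report should say so.

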##### Physical activity

Physical activity is assessed using physical activity monitors. The ‘Bodymedia Sensewear’ (APC Cardiovascular, UK) activity monitor is a biaxial accelerometer that can report a number of parameters including step count and energy expenditure. We will also use these data to assess compliance to the physical activity recommendation of undertaking at least 150 min of moderate intensity physical activity per week in bouts of at least 10 mins. Participants are asked to wear the activity monitor on the back of their right arm for seven consecutive days (24 hours a day if possible) following their baseline, 6-month and 9-month visits.

#### Questionnaires

##### Health-related quality of life (HRQOL)

HRQoL data will be measured using the European Quality of Life-5 Dimensions (EQ-5D^20 21^). The EQ-5D is a standardised questionnaire that was developed for use as a measure of health outcomes and defines health in terms of five dimensions: mobility, self-care, usual activities, pain or discomfort and anxiety or depression.

##### Self-reported Chronic Respiratory Questionnaire

Disease-specific HRQoL will be measured by the self-administered standardised CRQ-SR.^22^ An individual change of at least 0.5/domain (dyspnoea, fatigue, emotional functioning and mastery) is considered clinically important.^23^ There is both an initial and follow-up version depending on time of administration.

##### Anxiety and depression

Depression and anxiety will be measured using the Hospital Anxiety and Depression (HADS) Scale to produce independent subscales for anxiety and depression.^24^ The HADS is a self-report rating scale of 14 items on a 4-point Likert scale range (0–3). The HADS is a validated and a widely used questionnaire for screening for the separate dimensions of anxiety and depression and possible occurrence of anxiety and depression from patients^25^ and the general population.^26^ It measures anxiety and depression (seven items for each subscale). Cronbach’s coefficient was 0.884, which indicates good reliability. Published cut-off scores for clinically relevant indications of depression and anxiety recommend a score of 8 for each subscale.^27^

##### Patient activation

Patient activation (participants’ knowledge, skill and confidence for managing their own health and healthcare) will be measured using the Patient Activation Measure.^28^ This is a 13-item patient-reported measure that has been validated in the UK as a powerful and reliable measure of patient activation. Participants indicate their level of agreement on a four-point scale (strongly disagree to strongly agree) and responses are added to yield a raw score between 13 and 52. The raw score is calibrated to an activation score between 0 and 100 (the higher the score the higher the level of activation), which is then used to classify participants into one of four levels of activation (level 1: low activation; level 4: high activation).

##### COPD knowledge

The Bristol COPD Knowledge Questionnaire will be used to understand patients’ informational requirements and understanding and their knowledge base of COPD.^29^ The questionnaire is comprehensive and goes into detail, regarding various aspects of COPD, for example epidemiology, signs and symptoms and exacerbations and treatment.

#### Outcomes to assess feasibility and acceptability of trial parameters

We will use the following outcomes to assess the feasibility and acceptability of trial parameters:

##### Screening

Defined as the number of packs sent out to patients from GP practices and assessed for eligibility using inclusion/exclusion criteria by a study researcher.

##### Eligibility

Calculated by dividing number of people screened for eligibility by those who meet the inclusion criteria.

##### Consent

Defined as the proportion of people with COPD who met inclusion criteria, and were therefore eligible, who went on to consent in writing to participate in the study.

##### Group characteristics

Group characteristics (eg, age, gender, GOLD stage, Medical Reseach Council (MRC) dyspnoea grade, exercise capacity, physical activity) will be compared between completers and non-completers.

##### Retention

Defined as the number of participants who remain in the study and do not drop-out.

##### Study completion

Defined by the number of participants who complete the CAT at 6-months. Completion rates will be calculated at baseline, 6-month and 9-month follow-up.

#### Intervention adherence and completion rates

This will be measured by summing the total number of self-management programme sessions attended by participants allocated to the intervention group. We will also look at the average group size across each of the six self-management programme sessions and compare with the number of participants allocated to each of the self-management programme groups.

### Qualitative data collection

Those participants allocated to the intervention group are invited to take part in qualitative focus groups at the end of the SPACE for COPD(C) intervention. Focus groups have been chosen due to their generation of information on collective views and the meanings that lie behind those views. The aim of the focus groups will be to understand participants’ experiences of the group-based self-management programme. More specifically, the data we collect will inform:Acceptability and usefulness of the programme to participants in this format and over this time period;The content of the intervention;Approaches to recruitment.

Focus groups will be conducted with each self-management programme group, with between 3 and 10 participants (number dependent on each group size). This difference in participant numbers allows for participant opinions to be gathered even if a small group is encountered (eg, due to drop-out). Although three is a very small number for a focus group, it allows all participant opinions to be gathered, regardless of group size. Participants will be familiar with one another (which can help facilitate discussion or the ability to challenge each other comfortably) as they have attended multiple group sessions together. Purposive sampling will be employed to recruit intervention participants. Audio-recorded focus group discussions (approximately 60 min) will be conducted face-to-face between each participant group, an experienced interviewer and an observer/note-taker. Focus groups will be carried out at the end of the last group session for participant ease, as discussed with study patient representatives. We will prompt participants allocated to each self-management group of the focus group discussion prior to the last session in the attempt to gain experiences from as many participants as possible, regardless of the number of sessions attended in total. Focus groups will be transcribed verbatim by a professional transcriber, with identifiable information removed. Focus group questions have been devised based on relevant literature and experience of the team.

HCPs delivering the SPACE for COPD self-management support intervention will be invited to participate in a meeting to discuss aspects of feasibility and acceptability, such as gaining insight into any potential facilitators/barriers to implementing the intervention in practice (and derive practical recommendations for doing so). Minutes will be taken during the discussion and anonymised.

### Data analysis

#### Study power

The power calculation was based on the primary outcome at 6 months.^30 31^ To detect a mean±SD between-group difference of 2.5±5.0 in the change in CAT with 80% power, 60 people per group are required (α=0.05, two tailed). In anticipation of a possible 25% attrition rate, the total sample size was increased to 75 per group (150 in total).

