## Methods/design

### Study design

The trial is a prospective, multi-site, single (assessor) blinded randomised controlled trial comparing a community-based, HCP-led, group-based self-management programme based on the SPACE for COPD(C) manual with usual care. The design of the study and flow of participants is described in figure 1. The study will be run across Leicestershire and Rutland, and a total of 150 participants will be recruited (75 in the intervention group and 75 in the control group).

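### 75 per group does not absorb 25% attrition and 60 per group falls short of 80% power, so power at the planned attrition is about 75%

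*Protocol article*

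**What the plan says.** The calculation is in the protocol article under Data analysis, Study power. The base requirement reads: "To detect a mean±SD between-group difference of 2.5±5.0 in the change in CAT with 80% power, 60 people per group are required", with alpha given as 0.05, two tailed. The allowance for loss follows: "In anticipation of a possible 25% attrition rate, the total sample size was increased to 75 per group (150 in total"). The Study design section gives the same total: "a total of 150 participants will be recruited (75 in the intervention group and 75 in the control group"). Allocation is 1:1 (Randomisation). The Quantitative analysis section names t-tests and analyses of variance as examples of the methods. The power statement mentions no covariate adjustment, baseline correlation or other reduction in variance.

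**The concern.** The two numbers that justify the trial's size, 60 evaluable and 75 randomised per group, should follow from the stated difference, SD, alpha, power and attrition. Neither does. The 75 appears to come from adding 25% to 60, which is not the same as allowing for 25% of those randomised to be lost. The 60 is a few patients below what the standard two-sample formula gives.

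What is at stake is the stated power for the primary outcome. If the anticipated loss occurs, the chance of missing a true 2.5-point effect is about one in four, not the one in five that the protocol implies. Anyone who weighs a non-significant primary result against the planned power would credit the trial with more than its design delivers.

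**Working it through.** **Inputs.** All are from Study power, except the allocation ratio (Randomisation).

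- Difference in change in CAT: 2.5 points
- SD, read as the SD of the change: 5.0 points, so the standardised difference is 2.5/5.0 = 0.5
- Alpha 0.05, two-sided; power 80%; allocation 1:1
- Attrition 25%; evaluable 60 per group; randomised 75 per group

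**Step 1: try to reproduce 60.**

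- Normal approximation: n = 2 × (1.96 + 0.8416)² × (5.0/2.5)² = 62.8, so 63 per group.
- Two-sample t-test: the solution is 63.8, so 64 per group.
- Variants: one-sided alpha 0.05 gives 50 (normal). A target of 78% power gives 60 (normal) or 61 (t-test). At 80% power and two-sided 0.05, the printed inputs do not give 60.
- Power at 60 per group: 78.2% (normal) or 77.5% (t-test).

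**Step 2: reproduce 75.**

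- 60 × 1.25 = 75, which is the protocol's figure.
- Check: 75 × 0.75 = 56.25, which is below 60.
- Correct inflation of the stated base: 60/(1 − 0.25) = 80 per group.
- Loss that 75 actually absorbs on a base of 60: 1 − 60/75 = 20%.
- Correct inflation of the corrected base: 64/0.75 = 85.3, so 86 per group.
- Loss that 75 absorbs on a base of 64: 1 − 64/75 = 14.7%, or about 15%.

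**Step 3: power delivered by 75 randomised per group** (t-test, unadjusted comparison of change, lost patients contributing nothing).

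| Loss | Evaluable per group | Power |
|---|---|---|
| 0% | 75 | 86.0% |
| about 15% | 64 | 80.1% |
| 20% | 60 | 77.5% |
| 25% | 56 | 74.6% |

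The normal formula gives 75.4% at 56 per group. By the t-test, the difference detectable with 80% power at 56 per group is 2.67 CAT points.

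**Step 4: effect of adjusting for baseline CAT.** Assume equal variances at baseline and 6 months and correlation r between them. If the SD of change is 5.0, the variance at either time is 25/[2(1 − r)]. The residual variance after adjustment is that variance times (1 − r²), which equals 25(1 + r)/2. The protocol gives no value for r, so the range below is an assumption.

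- r = 0.5: residual variance 18.75, SD 4.33, power at 56 per group 85.7%
- r = 0.8: residual variance 22.5, SD 4.74, power at 56 per group 78.9%

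**The case against.** The case for leaving the statement alone does not dispute the arithmetic. It makes four points about weight.

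- **The base-size error is small.** The gap is 3 or 4 patients and about 2 power points. The inputs are printed to one decimal. If both were rounded in the favourable direction (difference just under 2.55, SD just over 4.95), the normal formula would give 60. This is fair as far as it goes, but it is a corner case and the t-test would still need 61. It makes the base size the secondary error and leaves the attrition error untouched, since 60 and 25% are all that is needed to show that 75 is too few.
- **The 75% is conditional.** It applies if the full 25% is lost, those lost contribute nothing, and the analysis is unadjusted. That is true, and the condition should be stated with the figure. But 25% is the loss that the protocol itself chose to plan for.
- **The Quantitative analysis section provides for imputing missing data and adjusting for baseline differences.** Neither is credited in the power statement. Imputation does not clearly restore the lost information. Adjustment that depends on observed imbalance is not a prespecified covariate analysis. A prespecified one would recover most or all of the shortfall, but at r = 0.8 power remains just under 80%.
- **The consequence is modest.** No estimate is biased, the type I error is unaffected, and a null result should be read from its confidence interval. This stands, and it bears on how serious the error is. It does not make the stated figures right.

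**Conclusion.** The statement is wrong as written. The main error is in the attrition step and needs no choice of test: 75 per group covers a 20% loss on the protocol's own base of 60, not the 25% it claims. The second, smaller error is the base itself, which should be 64 by the t-test (63 by the normal approximation).

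Together they put power at 74.6% instead of 80% at the planned attrition, and 80% power holds only up to about 15% loss. These figures rest on reading 5.0 as the SD of the change in CAT, on an unadjusted two-sample comparison, and on treating lost participants as contributing no information. With lower attrition or a prespecified baseline adjustment, the shortfall shrinks or disappears, but the power statement relies on neither.

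**What to change.** Keep 150 patients and restate the justification under Study power:

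- 64 evaluable patients per group are needed for 80% power to detect 2.5 points with SD 5.0 at two-sided alpha 0.05.
- 75 randomised per group with 25% attrition leaves about 56 evaluable per group and about 75% power; 80% power is kept up to about 15% attrition.
- If the primary analysis is prespecified to adjust for baseline CAT, give the power on that basis with the assumed baseline to 6-month correlation and its source. At 56 per group it would be about 79% for a correlation of 0.8 and about 86% for 0.5.

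The cost is wording in the protocol or SAP and a slightly less favourable stated power. No extra patients are needed. For reference, keeping 80% power at 25% attrition without adjustment would take 86 per group (172 in total).
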